**[name], MD**

Department of Obstetrics and Gynecology

Table of Contents

[Abstract 5](#_Toc497206426)

[Introduction 6](#_Toc497206427)

[Literature review 7](#_Toc497206428)

[Diagnosis of preeclampsia 7](#_Toc497206429)

[Management of preeclampsia 8](#_Toc497206430)

[Administration of magnesium sulphate 9](#_Toc497206431)

[Springfusor and flow control tube 10](#_Toc497206432)

[Statement of the problem 12](#_Toc497206433)

[Justification 13](#_Toc497206434)

[Research questions 14](#_Toc497206435)

[Methods 15](#_Toc497206436)

[Setting: 15](#_Toc497206437)

[Trial design: 16](#_Toc497206438)

[Study participants: 16](#_Toc497206439)

[Intervention 16](#_Toc497206440)

[Sample size 17](#_Toc497206441)

[Randomisation 17](#_Toc497206442)

[Trial flow chart 19](#_Toc497206443)

[Study procedure 19](#_Toc497206444)

[Adverse Events Reporting 20](#_Toc497206445)

[Outcome Measures 22](#_Toc497206446)

[Data management 24](#_Toc497206447)

[Safety and monitoring 26](#_Toc497206448)

[Ethical consideration 28](#_Toc497206449)

[**Informed Consent** 29](#_Toc497206450)

[Participant confidentiality 29](#_Toc497206451)

[Benefits to participants 29](#_Toc497206452)

[References 31](#_Toc497206453)

Abbreviations

BP Blood pressure

DSMB Data safety and monitoring board

gm grams

FCT Flow control tube

HELLP Hemolysis elevated liver enzymes Low platelet

IM Intramuscular

IV Intravenous

Ml millilitres

MFM Maternal foetal medicine

MgSO4 Magnesium sulphate

PE/E Preeclampsia/Eclampsia

SAE Severe adverse events

WHO World health organisation

Operational definition

1. Acceptability of the Springfusor: assessed using a likert scale ranging from 1 very acceptable, 2 acceptable, 3 neutral 4 unacceptable and 5 very unacceptable. Participants who scored 2 or less on the Likert scale are categorized as having considered springfusor acceptable. Participants who score 3 or more are considered to have found the Springfusor device unacceptable.
2. Safety of Springfusor: During the administration of magnesium sulphate, safety of use of Springfusor will be assessed by evaluating the possible occurrence of magnesium sulphate toxicity. This will be assessed by occurrence of any of the following; respiratory depression<16/min, respiratory arrest, depressed patellar reflex, liver failure, renal failure, cardiac arrest, and need for calcium gluconate.
3. Springfusor pump: Is a device powered by the potential energy stored within a spring that provides a constant force to the barrel of the loaded syringe.

# Abstract

**Introduction:** Magnesium Sulphate is the drug of choice for prevention and treatment of seizures in preeclampsia and eclampsia. It is administered parenterally by intravenous (IV) and or intramuscular (IM) routes. The IM regimen used in low resource settings, requires repeated painful injections which may be a barrier to optimal utilization whereby, there is frequent omission of some doses or increased interval between maintenance doses and low patient acceptability of magnesium. In addition, the IM regimen may potentially lead to abscess formation. There is a need to test an alternative way of providing Magnesium Sulphate that avoids the adverse events of IM regimens.

**Objective:** To assess the acceptability and safety of Springfusor device in the administration of magnesium sulphate in preeclampsia and eclampsia.

**Methods:** The study will be open label clinical randomized trail conducted at Mulago national referral and teaching hospital, where, 482 women diagnosed with preeclampsia and eclampsia will be randomized in blocks to either Springfusor device or standard of care for the administration of magnesium sulphate. Women in the Springfusor group will have their loading dose (4 gm of 50% Magnesium sulphate in 10 ml syringe administered over 20 minutes) and maintenance therapy (4 gm of 50% Magnesium sulphate in 10 ml syringe administered over 4 hours. The 4 gm maintenance dose will be repeated every 4 hours for 24 hours) of Magnesium sulphate through an IV infusion administered using a Springfusor pump. The control group will have Magnesium sulphate administered according to the Pritchard regimen (standard hospital practice). The Pritchard regimen involves administration of loading dose of 4 gm of 20% Magnesium sulphate IV over 15-20 minutes, immediately followed by 10 gm of 50% Magnesium sulphate IM (5gm on each buttock). The maintenance dose of 5 gm of 50% Magnesium sulphate IM every 4 hourly in alternate buttocks continued for 24 hours.

The primary outcome is the acceptability of administration of Magnesium sulphate using Springfusor assessed using a Likert scale. The other outcomes are discontinuation and complications in the two arms. Analysis will be intention to treat.

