## Research questions

1. Acceptability:
   1. What is the overall acceptability of Springfusor use among women with preeclampsia and eclampsia?
   2. What is the acceptability of the springfusor use for magnesium sulphate administration among health providers
   3. What is the level of pain associated with using Springfusor compared to the standard of care in administration of magnesium sulphate?
2. Effectiveness of Springfusor:
   1. What is the discontinuation rate of magnesium sulphate administration using a Springfusor pump compared to standard of care?
3. Safety
   1. What is rate of complications in the two arms?

Hypothesis

Use of Springfusor pump in the administration of magnesium sulphate in women admitted with preeclampsia and eclampsia is more acceptable than the hospital standard practice

Objectives

Primary objective

1. To compare the acceptability of the Springfusor pump to the standard of care in the administration of magnesium sulphate.

Secondary objective

1. To compare the proportion of complications between the Springfusor pump and the standard of care groups
2. To determine level of pain associated with using Springfusor compared to the standard of care?
3. To determine the discontinuation rate of administration of magnesium sulphate among women admitted with preeclampsia and eclampsia
4. To assess the reliability of Springfusor pump in the delivery of magnesium sulphate when used repeatedly
5. To assess the acceptability of the Springfusor pump for the administration of magnesium sulphate among the health providers.

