### Intervention

Women in the intervention arm (Springfusor group) will have their loading and maintenance therapy of magnesium sulphate using IV infusion administered using a Springfusor infusion pump. The loading dose will be 4 gm of 50% magnesium sulphate in 10 ml syringe administered over 20 mins. The maintenance dose of 4 gm of 50% magnesium sulphate in 10 ml will administered over 4 hours. The 4 gm dose will be repeated every 4 hours for 24 hours

Women in the control arm (Standard of care group) will have magnesium sulphate administered according to the standard hospital practice. The loading dose of is administered using an IV-push in which health worker manually and slowly inject 4 gm of 20% Magnesium sulphate in 20 ml syringe over 15-20 minutes. This is immediately followed by IM injection of 10 gm of 50% magnesium sulphate and 1 ml of lignocaine into the gluteal muscles (5 gm on each buttocks). The maintenance dose of 5 gm IM injection every 4 hourly for 24 hours. Over the 24 hour period the intravenous group (intervention) would have got 28 gm of magnesium sulphate while the intramuscular group (control) would have received 39 gms. The higher total dose in the control group is assuming a reduce bioavailability of intramuscular drug.

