### Outcome Measures

Primary outcome:

- Acceptability of Springfusor for administration of magnesium sulphate will be assessed using a Likert scale ranging from one (very acceptable) to five (very unacceptable). The method of magnesium sulphate administration is regarded acceptable if its rated 1 and 2 on the likert scale. It is not acceptable if the ranking is three and above. Women who discontinue the method of administration by choice or due to side effects will be considered in group of unacceptable.

Secondary outcomes:

- *Rate of complications of preeclampsia and its management:* Proportion of preeclamptic women who developed magnesium sulphate toxicity, abnormal liver and renal function test as reported by the laboratory report, infection at the injection as reported by the clinician and maternal deaths
- Discontinuation: This will be assessed as study participants who do not completed doses of magnesium sulphate in 24 hour period of including the loading dose. Participants who discontinue the method of administration by choice, due to side effects or by health workers decision will be considered in group. This will be measured by the number of dose received for each arm. For the Pritchard arm (standard of care), the number of complete 6 doses equivalent to 29 gm (including loading dose) in 24 hours. In the Springfusor, the number of complete 6 doses equivalent to 24 gm (including loading dose) in 24 hours.
- *Level of pain:* The study participants will be asked to assess the severity of pain during the administration of magnesium sulphate using Visual analogue scale 1-7. The least (one) representing no pain and maximum (7) representing the worst pain imaginable.
- Safety of use of Springfusor will be assessed by evaluating the possible occurrence of magnesium sulphate toxicity. This will be assessed by occurrence of any of the following
  - respiratory depression<16/min,
  - respiratory arrest,
  - depressed patellar reflex,
  - liver failure, renal failure,
  - cardiac arrest,
  - a need for calcium gluconate.
- In addition, other side effects of magnesium sulphate like nausea, vomiting, flushing of the skin, muscle weakness, confusion and drowsiness will be noted.

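### The discontinuation outcome mixes women whose treatment was stopped with women who finished six doses late, and its six-dose, 24-hour rule does not fit the courses described under Intervention

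*Protocol*

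**What the plan says.** As background, the Protocol's Abstract describes the effect of painful intramuscular injections as "frequent omission of some doses or increased interval between maintenance doses".

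The Protocol's Research questions section puts one question under effectiveness: "What is the discontinuation rate of magnesium sulphate administration using a Springfusor pump compared to standard of care". The outcome that answers it is defined in Outcome Measures, in three parts that do not fully agree.

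- A clock rule: discontinuers are "study participants who do not completed doses of magnesium sulphate in 24 hour period of including the loading dose".
- A reason rule: "Participants who discontinue the method of administration by choice, due to side effects or by health workers decision will be considered in group".
- A measure with thresholds: "This will be measured by the number of dose received for each arm". For the Pritchard arm the threshold is "the number of complete 6 doses equivalent to 29 gm (including loading dose) in 24 hours", and for the Springfusor arm "the number of complete 6 doses equivalent to 24 gm (including loading dose) in 24 hours".

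The Intervention section describes the courses. The Springfusor arm gets 4 gm over 20 minutes, then 4 gm over 4 hours, repeated every 4 hours for 24 hours. Its stated total is: "Over the 24 hour period the intravenous group (intervention) would have got 28 gm of magnesium sulphate". The control arm gets 4 gm IV plus 10 gm IM as loading, then 5 gm IM every 4 hours for 24 hours, with a stated total of 39 gm.

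On timing data, Study procedure has the loading dose timed, and the maintenance dose timed by stop clock for the Springfusor. It names no clock time for the maintenance injections.

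**The concern.** A woman who receives all six doses but completes the sixth after 24 hours fails the clock rule. She matches none of the listed reasons: she did not choose to stop, had no side effect that stopped her, and no health worker ended the course. The definition has no other place for her, so on its literal wording she is a discontinuer. Elsewhere the Protocol uses the word for giving treatment up: Statement of the problem speaks of patients who stop maintenance because the injections hurt.

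This matters because lateness has a different source in each arm. In control it comes from when the staff give the injection. On the Springfusor it comes from flow rate and the time needed to reload. A difference in discontinuation could therefore reflect ward punctuality or pump speed rather than women or staff stopping treatment. It is the only measure listed under the effectiveness question.

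The six-dose threshold also does not ask the same of both arms when set against the courses in the Intervention section.

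**Working it through.** All dose and time inputs come from Intervention and Outcome Measures in the Protocol. Time runs from the start of loading, and control loading (IV plus IM) counts as one administration.

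**1. Gram totals**

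- Springfusor, six doses: 6 × 4 = 24 gm. This reproduces the threshold in Outcome Measures.
- Springfusor, Intervention total: 4 + 6 × 4 = 28 gm. This is seven doses.
- Control, Intervention total: (4 + 10) + 5 × 5 = 39 gm. This is six administrations.
- Control, Outcome Measures threshold: 29 gm for six doses does not reproduce from the full loading dose. It results if the 10 gm IM part of loading is left out (4 + 5 × 5 = 29), or with the full loading dose and only three maintenance doses (14 + 3 × 5 = 29), which is four administrations.

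**2. On-schedule finish and slack under the six-dose, 24-hour rule**

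- Springfusor: 20 min + 5 × 240 min = 1,220 min = 20 h 20 min. Slack is 1,440 − 1,220 = 220 min = 3 h 40 min. Over five maintenance infusions that is 44 min each, or 44/240 = 18.3% of the planned infusion time, with reloading included.
- Control: the fifth maintenance injection is due at 5 × 4 = 20 h. Slack is 4 h, or 48 min for each of five intervals. If intervals run instead from the end of a 20-minute IV push, slack is 3 h 40 min.

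**3. The full courses against the same clock**

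- Springfusor, seven doses: 20 + 6 × 240 = 1,460 min = 24 h 20 min, before any reloading time. At exactly 24 h, 4 + 4 × (1,420/240) = 27.67 gm would have run in.
- Control, six administrations: the last is due at 20 h, inside the window.

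| | Springfusor | Control |
|---|---|---|
| Doses in the Intervention course | 7 | 6 |
| Doses required by the outcome | 6 | 6 |
| Full course on schedule | ends 24 h 20 min | last due 20 h |
| Grams, Intervention | 28 | 39 |
| Grams, Outcome Measures | 24 | 29 |

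**4. Illustration only**

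The Protocol gives no rate of late dosing, so the inputs here are assumed. Every woman receives all six doses, and delays accumulate.

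- Control: five gamma-distributed delays with SD 30 min each, reclassified if their sum exceeds 240 min. Mean delays of 20, 30 and 45 min give about 4%, 10% and 38%.
- Springfusor: 5 min to reload and SD 15 min per cycle, normal approximation, reclassified if the sum exceeds 220 min. Infusions lasting 10%, 15% and 20% longer than planned give mean total delays of 5 × (5 + 24) = 145, 5 × (5 + 36) = 205 and 5 × (5 + 48) = 265 min, hence about 1%, 33% and 91%.

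The spread from 1% to 91% shows that the result depends almost entirely on the assumed inputs.

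**The case against.** The 24-hour window is not arbitrary. It is the planned treatment period in both arms, and the Protocol describes no catch-up dosing after it. Doses delivered within the intended period is a legitimate measure of effectiveness. This stands: the window is not wrong in itself. What does not follow is calling a late finish discontinuation.

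The slack is generous, so one modestly late dose changes nothing. This also stands and limits the point to substantial cumulative delay.

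A slow pump would be visible anyway, because infusion times are measured and reliability within the prescribed time is a separate outcome. That is true for the Springfusor arm, but no parallel timing is named for the maintenance injections. The primary outcome is unaffected: its own rule covers only women who stop by choice or because of side effects.

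Scoring without any clock would hide under-treatment in a woman dosed at much longer intervals. This is fair, and it is why timing should be reported alongside stopping rather than dropped.

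A reader might infer two stronger claims. One is that the Protocol contradicts itself by treating omitted doses and longer intervals as different problems. The Abstract and Introduction do not support this: they join the two with an or, as two results of the same barrier, and promise no separate outcomes. The other is that every Springfusor woman would be a discontinuer. That would need the seven-dose course to be put into the outcome while the 24-hour limit is kept, which the Protocol does not do. As written, its threshold is six doses, reached on schedule at 20 h 20 min.

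An SAP that is not shown could refine the scoring, but the Protocol itself fixes this definition.

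**Conclusion.** The point holds in a limited form. The discontinuation outcome classes a woman who finishes six doses after 24 hours with women whose treatment was stopped, although she fits none of its listed reasons. Reclassification needs more than about 3 h 40 min of cumulative delay on the Springfusor, or about 4 h in control with intervals counted from the start of loading. The causes of such delay differ between arms, so the comparison can be distorted in either direction. The number of women affected cannot be computed from the Protocol.

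Separately, and by arithmetic alone, the six-dose rule equals the full control course by count but is one infusion short of the 28 gm Springfusor course. The gram totals in Outcome Measures (24 and 29) also disagree with those in Intervention (28 and 39). These passages must be reconciled, and nothing here says which is right. One secondary outcome is affected.

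**What to change.** In Outcome Measures, score discontinuation as the course being stopped before its planned last dose, with the recorded reason. Report two timing measures separately for each arm: the number of doses received within 24 hours, and the time from loading to the last dose. Record the clock time of each injection on the CRF so that the control arm has timing data comparable to the Springfusor arm. Injection times not recorded during treatment cannot be reliably recovered later.

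At the same time, reconcile the dose counts, gram totals and time limit in Outcome Measures with the course in the Abstract and Intervention sections. The two changes belong together, because the planned last dose is not defined until those sections agree. Changing the count to seven while keeping the 24-hour limit would put even an undelayed Springfusor course 20 minutes past the limit.

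The cost is the rewording of one secondary outcome, one more CRF field and one more reported measure. No change to dosing is proposed.

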# Introduction

Preeclampsia is a disorder that presents with a raised blood pressure and proteinuria in pregnancy through to postnatal period [[1](#_ENREF_1)]. Globally, preeclampsia complicates approximately 2-8% of the pregnancies [[2](#_ENREF_2)] The presence of convulsions with preeclampsia indicates eclampsia, however, occasionally seizures may occur in the absence of hypertension and/or proteinuria . Preeclampsia and eclampsia (PE/E) are life-threatening for both the mother and the fetus. Preeclampsia and eclampsia are among the leading causes of maternal deaths and disability worldwide, more especially in the low resource setting [[2](#_ENREF_2)]. The World Health Organization (WHO) estimates that, 16% of the maternal deaths in low resource settings are due to PE/E [[3](#_ENREF_3)]. According to 2016 annual report of Mulago National teaching hospital, PE/E ranked second to hemorrhage as a specific, direct cause of maternal deaths, accounting for 21% of the maternal deaths (.

Magnesium Sulphate is the drug of choice for prevention and treatment of Eclampsia [[3](#_ENREF_3)]. It is administered parenterally by intravenous (IV) and or intramuscular (IM) routes. The IV regimen achieves more stable serum levels of Magnesium Sulphate but requires the use of electronic infusion pump for safe delivery. In low resource settings, electric infusion pumps are not available or feasible. The IM regimen used in low resource settings, requires repeated painful injections which may be a barrier to optimal utilization whereby, there is frequent omission of some doses or increased interval between maintenance doses and low acceptability of magnesium sulphate. In addition, the IM regimen may potentially lead to abscess formation. There is a need to develop an alternative way of providing Magnesium Sulphate that avoids the adverse events of IM regimens that can be used in low resource settings.

# Literature review

Preeclampsia is one of the hypertensive disorders that complicates approximately 2-8% of the pregnancies [[2](#_ENREF_2)]. It is one of the leading causes of maternal and neonatal morbidity and mortality worldwide [[4](#_ENREF_4)]. Preeclampsia may affect the liver, the kidney, blood coagulation and the brain. When there is delay in control of hypertension and or termination of pregnancy, preeclampsia may progress to placental insufficiency and maternal organ dysfunction.

The risk to the fetus is due to reduced or inadequate blood supply because of the damaged placenta, where it may lead to intrauterine growth restriction and fetal demise. In addition, management of preeclampsia may require women to have an early delivery (to protect the mother or fetus from injury), which leads to premature births. Severe preeclampsia may lead to seizures (eclampsia) [[5](#_ENREF_5)]. However, women can develop eclampsia without severe disease.

## Diagnosis of preeclampsia

Preeclampsia is a multisystem disease characterized by hypertension accompanied by proteinuria. The new onset of hypertension after 20 weeks of pregnancy (a systolic BP of >140 mmHg or a diastolic blood pressure >90 mmHg), with the new occurrence of proteinuria (>0.3g/24 hours) is the criteria for diagnosis of preeclampsia [[1](#_ENREF_1)]. Preeclampsia is usually classified as non-severe or severe [[3](#_ENREF_3)]. Progression to severe can be fast, unanticipated and fulminant. Preeclampsia is not considered severe until systolic or diastolic blood pressure exceed 160 mmHg or 110 mmHg respectively [[6](#_ENREF_6)]. The American College of Obstetricians and Gynaecologists recommend that the diagnosis of hypertension requires at least two measurements of blood pressure taken 4 hours apart, however when the blood pressures are severe, the diagnosis can be confirmed within minutes to enable timely antihypertensive therapy [[1](#_ENREF_1)]. It is also recommended that the diagnosis of proteinuria is when a 24 hour excretion equals or exceeds 300 mg/l. However, when a quick decision is require or the facility is not able to perform 24 hour protein estimation, a urine dipstick reading of 1+ is suggestive of proteinuria [[1](#_ENREF_1)].

Women with mild preeclampsia usually are asymptomatic. However those with severe preeclampsia may have headache, blurring of vision and abdominal pain (epigastric). Maternal organ dysfunction associated with severe preeclampsia may present with HELLP syndrome (hemolysis, elevated liver enzymes and low platelets), eclampsia, stroke and disseminated intravascular coagulation [[2](#_ENREF_2), [3](#_ENREF_3)]. Leeman and colleagues have indicated that the presence of the following are features of severe preeclampsia; elevated creatinine level (>1.1mg/dl), hepatic dysfunction (transaminase levels > 2 times upper limit of normal or right upper quadrant or epigastric pain, new onset of headache or visual disturbance, pulmonary oedema and or platelet count < 100x10^9^ per l [[6](#_ENREF_6)]

